### Intervention group: Intensive treatment plus facilitator led behaviour change intervention

Participants in this group received intensive treatment (described above) plus a facilitator-led, individually tailored behaviour change intervention, based on psychological theory and evidence. The intervention was delivered by trained lifestyle facilitators, who were not part of the practice team. The facilitators used detailed protocols for each contact with the participant and received on-going supervision and feedback from a Clinical Psychologist, informed by assessment of tape-recorded consultations, enabling tight quality assurance of intervention delivery. The intervention was designed to build on the diabetes education delivered by practice nurses and intensive treatment by the practice team. The behaviours targeted in the intervention were physical activity, dietary intake, medication adherence, and smoking cessation. Hypothesised mediators of behaviour change targeted in the intervention included illness perceptions based on Leventhal's Common-Sense Model [41] and beliefs about behaviour change based on the Theory of Planned Behaviour (TPB) [29]. The intervention targeted instrumental (e.g. health) and affective beliefs about changing specific behaviours, (lack of) encouragement by important others (subjective norm), and perceived barriers and facilitators of behaviour change (perceived behavioural control). The behaviour change techniques used by the facilitators could be mapped onto the TPB (e.g., giving information, strengthening motivation), Operant Theory (identifying cues for action and reinforcement of behaviour change or effort), Carver and Scheier's Control Theory (e.g., goal setting, action planning, self-monitoring) and Relapse Prevention Theory (e.g., preparing for and dealing with setbacks) [29,43-45]. Facilitators taught patients this range of self-regulatory skills to achieve behaviour change and maintenance over time, which was supported by a manual describing the skills. Each patient initially selected to work on the behaviour(s) they most wanted to change and felt most confident about changing. The facilitator later discussed with them other domains in which change was possible and encouraged patients to consider setting additional goals. Interested patients were offered pedometers and/or glucometers. The intervention was delivered over one year at the participants' surgeries. It included a one-hour introductory meeting followed by six 30-minute meetings and four brief phone calls. Facilitators visited participant's homes or workplaces if it was not possible to meet in the surgery.

### Measurement

Table 1 shows the measures taken at each stage in the *ADDITION-Plus *study. Baseline measurements were carried out on all eligible patients including the completion of questionnaires, physiological and anthropometric measures, and venesection. Similar measurements were conducted one year after recruitment. Measurements were undertaken at outpatient clinical research facilities by trained staff following standard operational procedures and unaware of participants' study group allocation. Double data entry of all anthropometric and questionnaire measures was undertaken by experienced, independent agencies, blind to study group (Wyman Dillon Research and Data Management, Bristol, UK and Document Technologies and Imaging Solutions Ltd, Chalgrove, Oxford, UK).

#### Objectively measured health behaviours

Physical activity was assessed at one-year using a combined heart rate and movement sensor (Actiheart, CamNtech, Cambridge, UK), which was worn continuously for at least 4 days [46]. A graded treadmill walk test was used for individual calibration of heart rate [47], a procedure which also provides an estimate of cardio-respiratory fitness by extrapolation of the HR-VO2 relationship to age-predicted maximal heart rate [48]. Heart rate data collected during the free-living period were pre-processed [49] and activity intensity (J/min/kg) was estimated using a branched equation framework [47,50]. Resulting time-series data were summarised into physical activity energy expenditure (PAEE, in kJ/kg/day) and time spent in sedentary and moderate-to-vigorous intensity physical activity (SPA and MVPA, min/day), whilst minimising diurnal information bias caused by non-wear periods (segments of non-physiological data). Participants without individual calibration data but who provided data during free-living were processed using an age, sex, beta blocker, and sleeping heart rate adjusted group calibration equation for the translation of heart rate into activity intensity.

Dietary intake was assessed at baseline and one-year by plasma vitamin C levels. Vitamin C is not endogenously produced and therefore provides a robust measurement of consumption. Medication adherence was assessed at one-year by plasma drug levels. Concentrations of metformin, simvastatin and atorvastatin in plasma samples were measured by liquid-chromatography mass-spectrometry (LC-MS/MS) after protein precipitation extraction. The LC-MS/MS methods for simvastatin and atorvastatin were established at Quotient Bioresearch Ltd. (Fordham) for the *ADDITION-Plus *study. The metformin method was validated at Quotient Bioresearch Ltd. (Fordham) for a previous study [51]. The calibration ranges for each of the analytes were as follows: metformin 5.00-5000 ng/mL, simvastatin 0.100-50.0 ng/mL and atorvastatin 0.0600 to 30.0 ng/mL. Objective measurement of smoking was assessed by analysis of cotinine levels in plasma samples using an Immulite^® ^Nicotine metabolite solid phase competitive chemiluminescent immunoassay (Siemens).

#### Self-reported health behaviours

Physical activity was assessed using the validated EPAQ2 [52] and IPAQ [53] questionnaires. Dietary intake was evaluated using a validated food frequency questionnaire [54]. Medication adherence was assessed by the Medication Adherence Report Schedule (MARS) questionnaire [34]. Smoking status and alcohol consumption were assessed by questionnaire.

#### Modelled CVD risk

The UKPDS model [33] uses information on sex, ethnicity, smoking status, presence or absence of atrial fibrillation, systolic blood pressure, HbA_1c_, total cholesterol, and HDL-cholesterol to predict the 10-year risk of primary CVD. Predicted events include myocardial infarction, sudden cardiac death, other incident ischaemic heart disease, stroke, and peripheral vascular disease death.

#### Biochemical measures

HbA_1c _was analysed in venous samples at the time of diagnostic testing by ion-exchange high-performance liquid chromatography on a Tosoh machines (Tosoh Bioscience, Redditch, UK). Serum total cholesterol, HDL-cholesterol and triglycerides was measured by means of enzymatic techniques (Dade Behring Dimension analyser, Newark, USA). Plasma creatinine was analysed with kinetic colorimetric methods, and urine albumin by rate nephelemetry (Dade Behring Nephelometer II, Newark, USA). Plasma levels of urea and electrolytes, bilirubin, alanine aminotansferase (ALT), aspartate aminotransferase (AST), alkaline phosphatase, and thyroid stimulating hormone (TSH) and urine levels of creatinine were assayed by means of the Dade Behring Dimension analyser. Metaphosphoric acid was added to plasma samples for vitamin C analysis before being stored at -80C°. Plasma vitamin C level was measured with a Fluoroskan Ascent FL fluorometer. The albumin-to-creatinine ratio (ACR) was measured on a random spot urine specimen.

#### Clinical measures

Blood pressure was calculated as the mean of three measurements performed after at least 10 minutes rest, while participants were seated with the cuff on the predominant arm at the level of the heart, using an automatic sphygmomanometer (Omron M4, UK). ECG was recorded by a 12 lead machine. Body height and weight were measured in light indoor clothing and without shoes using a fixed rigid stadiometer and a scale (SECA, UK) respectively. Waist circumference was estimated as the average of two measurements taken with a tape measure halfway between the lowest point of the rib cage and the anterior superior iliac crests when standing. Body fat percentage was measured by bio-electrical impedance (TANITA, Tokyo, Japan). Angina was assessed using the Rose angina questionnaire [55]. Neuropathy was evaluated using an adapted version of the Michigan Neuropathy Screening Instrument [56].

#### Health utility, functional status, quality of life, well-being, treatment satisfaction and anxiety

The generic and disease-specific instruments used were diabetes well-being questionnaire (W-BQ12) [57], SF-36 [58], Audit of Diabetes-Dependent Quality of Life (ADDQoL) [57], diabetes treatment satisfaction (DTS) [57], and EuroQol (EQ-5D) [59], and the short form of the state scale of the Spiegelberger State-Trait Anxiety Inventory [60]. All patients completed the consultation and relational empathy (CARE) measure in relation to the GP and practice nurse; participants in the intervention group also completed this measure in relation to the lifestyle facilitator [61]. Participants were also asked to complete six items at one year asking about their views on the diabetes service they had received in the last 12 months, including frequency of contact, information and advice received, and satisfaction with the service. Participants were also asked about the frequency of and views about self-monitoring of blood glucose using the Diabetes Glycaemic Education and Monitoring (DiGem) study questionnaire [62].

#### Beliefs about behaviour change, illness perceptions, and habit

A questionnaire, developed according to TPB guidelines [29,63], assessed selected cognitions about becoming more physically active, eating a lower fat diet, taking medication and smoking: intention, perceived behavioural control, and behavioural beliefs. Each construct was assessed with two items, measured on a 5-point Likert-type scale ranging from 'strongly disagree' to 'strongly agree'. Examples of perceived control items are: 'I am confident that I could be more physically active/eat a lower fat diet in the next 12 months, if I wanted to'; for intention: 'I intend to be more physically active/eat a lower fat diet in the next 12 months'; and for behavioural beliefs: 'If I was more physically active/did eat a lower fat diet in the next 12 months, it is likely that I would lose weight'. We used the consequences and treatment control subscales (11 items) of the Illness Perception Questionnaire-Revised (IPQ-R) [64,65]. The consequences scale assessed seriousness of diabetes and the impact of diabetes on various aspects of life. An example is: 'My diabetes is a serious condition'. The treatment control scale assessed beliefs and feelings associated with the management of diabetes. An example is: 'My treatment can control my diabetes'. Both scales were measured on 5-point Likert-type scales ranging from 'strongly disagree' to 'strongly agree'. Participants were also asked to complete a nine-item closed-response questionnaire covering basic knowledge of diabetes and its' management [66]. At one year, participants were asked to write down the most important change that they had made in their physical activity and dietary intake, and 12 items were used to assess to what extent these changes had become a habit [67].

#### Intervention evaluation

Participants in the intervention group completed 10 items at one year about their views on the frequency of contacts with the lifestyle facilitators, clarity of advice given, educational materials, and overall intervention. They also completed a skills questionnaire assessing their confidence in relation to using nine skills (e.g., goal setting, action planning, self-monitoring) on a 10-point scale ranging from 'not at all confident' to 'very confident', and use of these skills in the past 11 months in order to increase physical activity, eat a lower-fat diet, try to stop smoking (if applicable) and try to take medicines regularly as prescribed (if applicable) on a binary scale (yes/no).

#### Costs

Health service use in the three months prior to follow-up was quantified using an adapted version of the Health Services Research Unit Aberdeen questionnaire that enquires about the use of services (consultations with healthcare professionals and hospitalisations) and medications [68].

### Participant safety

Treatment algorithms were developed with advice from local diabetes specialists who also contributed to the initial and follow-up practice-based training sessions for primary care staff involved in diabetes care. The responsibility for prescribing and management decisions remained with the general practitioners. Classes of medication were only recommended within licensed indications. Before taking part in the treadmill test, participants completed a pre-test screening questionnaire incorporating the Rose angina questionnaire. If they answered positively to any of the questions, a short medical review was completed by a clinical member of the team. Blood pressure, current medications and ECG (if available) were also reviewed following strict protocols before a participant was allowed to begin the treadmill test.

### Statistical analysis

The additional benefit of the facilitator-led behaviour change intervention on objective measures of physical activity level, medication adherence, and change from baseline in plasma vitamin C and smoking status will be assessed using an intention to treat analysis comparing the intervention and comparison groups, using linear regression for continuous outcomes and a comparison of proportions for binary outcomes. Continuous outcomes will be analysed with adjustment for the baseline value of the outcome, where this has been measured, in order to improve precision. Those participants missing the baseline value will remain included in the analysis by using the missing indicator method, which is valid for pre-randomisation measures in trials [69]. Due to the large number of stratifier categories, there will be no adjustment for stratifiers in order to ensure that estimation of intervention effects is stable. The modelled ten-year cardiovascular risk will be log transformed before analysis and computed for those with and without a history of previous CVD events. The primary intention to treat analysis will be supported by per protocol analyses of primary outcomes, where the per protocol population is defined to be those participants attending the introductory and initial three core intervention sessions. The impact of missing primary outcome data will be examined within sensitivity analyses using the multiple imputation method of Rubin [70]. This will involve fitting an imputation model from the observed data, from which missing data will be imputed under two opposing scenarios. In the first scenario it is assumed that the same full intervention-minus-comparison effect applies amongst participants with missing data as has been observed amongst their counterparts with observed data. In the second scenario it is assumed that the intervention-minus-comparison effect is zero for participants with missing data. Ten complete datasets will be imputed, as recommended, to incorporate the uncertainty in the residuals and parameter estimates of the imputation model. Subgroup analyses will be confined to the comparison of intervention effects on primary outcomes by the route of diagnosis (screen-detected versus already-diagnosed).

The perspective for cost analysis will be the health service and will include recent use of services (GP/hospital appointments & admissions) and prescribed medications in the previous 3 months. The costs of intensive treatment with and without the facilitator-led behaviour change intervention will be compared with unit change in health utility. In addition, costs at one-year and future costs derived from existing data [71] will be compared with risk of death and cardiovascular events, with appropriate sensitivity analysis.

Cohort analyses will be reported separately and will test causal pathways between behavioural determinants, behaviour change and consequences of behaviour change.

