***Objectively measured health behaviours***				

Physical activity (ActiHeart)[47]			X	X

Dietary intake (plasma vitamin C concentration)	X	X	X	X

Medication adherence (plasma drug concentrations)			X	X

Smoking status (plasma cotinine concentration)			X	X

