***Self-reported health behaviours***				

Physical activity: EPAQ-2 [52], IPAQ [53]	X	X	X	X

Dietary intake: EPIC food frequency questionnaire [54]	X	X	X	X

Medication adherence:				

All drugs during the last month [34]	X	X	X	X

Hypoglycaemic drugs during the last month [34]			X	X

Smoking status and alcohol consumption (questionnaire)	X	X	X	X

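### The sensor-measured primary activity outcome has no baseline value and so gets no covariate under the plan's rule, although baseline activity questionnaires exist in both arms: a missed gain in precision, not a bias

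*Protocol article*

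**What the plan says.** All references are to the protocol article.

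- **Adjustment rule (Statistical analysis).** "Continuous outcomes will be analysed with adjustment for the baseline value of the outcome, where this has been measured". The stated purpose is "in order to improve precision".
- **Other covariates (same section).** The minimisation factors are excluded: "there will be no adjustment for stratifiers in order to ensure that estimation of intervention effects is stable". No further covariate is named.
- **Missing baseline values (same section).** "Those participants missing the baseline value will remain included in the analysis by using the missing indicator method".
- **Timing of the primary activity measure (Objectively measured health behaviours).** "Physical activity was assessed at one-year using a combined heart rate and movement sensor". Table 1 agrees: its sensor row is blank at baseline and marked in both arms at one year.
- **Baseline activity data (Self-reported health behaviours).** "Physical activity was assessed using the validated EPAQ2 [52] and IPAQ [53] questionnaires". Table 1 marks both questionnaires at baseline and at one year, in both arms.
- **Randomisation (Participants).** The minimisation uses age, sex, practice, smoking, self-reported medication adherence and BMI. Physical activity is not a factor.
- **Sample size.** With 200 per arm followed up, 80% power and a 5% level, the detectable PAEE difference is 0.017 kJ/kg/min (SD 0.058, mean 0.078). For vitamin C the section gives 5.5 umol/l unadjusted and 4.0 umol/l after baseline adjustment, using a correlation of 0.67.

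**The concern.** The rule links adjustment to a baseline value of the same outcome. PAEE has none and the stratifiers are out, so as written the model for this primary endpoint contains treatment arm and nothing else. Yet the trial holds a pre-randomisation measure of the same behaviour in both arms. The rule's own purpose is precision, and a baseline questionnaire score could serve it. The reason given for omitting stratifiers, that there are too many categories, does not apply to a single score.

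Two things are at stake for PAEE. One is the width of its confidence interval. The other is protection against a chance difference between arms in how active people were at entry. The design does not balance activity directly, though minimising on age, sex and BMI may do so in part.

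**Working it through.** **Inputs.** From Sample size: n = 200 per arm, PAEE difference 0.017, SD 0.058, mean 0.078; vitamin C SD 19, correlation 0.67. The documents do not state sidedness, so a two-sided 5% test is assumed. The correlation r between the baseline questionnaire score and one-year PAEE is also not given. It is an assumption here, shown over a range.

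**Step 1: the plan's PAEE figure.** Detectable difference = (1.960 + 0.842) × SD × √(2/n) = 2.802 × 0.058 × 0.10 = 0.01625, or 20.8% of the mean. The plan states 0.017, and 0.017/0.078 = 21.8%, matching its 22%. For 0.017 the required n is 183 per arm. Power at 200 per arm is Φ(0.017/0.0058 − 1.960) = Φ(0.971) = 83.4%. The stated difference is therefore not reproduced exactly, but it errs on the cautious side, consistent with rounding up. It uses the unadjusted SD and takes no credit for a covariate.

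**Step 2: the plan's own adjustment logic.** For vitamin C, unadjusted: 2.802 × 19 × 0.10 = 5.32 (stated 5.5). Adjusted: 5.32 × √(1 − 0.67²) = 3.95 (stated 4.0). The plan's gain thus follows from residual SD = SD × √(1 − r²).

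**Step 3: the same formula for PAEE.** Power = Φ(2.931/√(1 − r²) − 1.960), and effective n = 200/(1 − r²).

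| Assumed r | Residual variance removed | Detectable difference | Power for 0.017 | Effective n per arm |
|---|---|---|---|---|
| 0 (plan) | 0% | 0.0162 | 83.4% | 200 |
| 0.1 | 1% | 0.0162 | 83.8% | 202 |
| 0.2 | 4% | 0.0159 | 84.9% | 208 |
| 0.3 | 9% | 0.0155 | 86.7% | 220 |
| 0.4 | 16% | 0.0149 | 89.2% | 238 |
| 0.5 | 25% | 0.0141 | 92.3% | 267 |

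**Step 4: chance imbalance.** The between-arm difference in a baseline score has standard error √(2/200) = 0.10 SD. Only r times that difference carries into the PAEE estimate. At r = 0.2 to 0.4 the carried part has a standard error of 0.02 to 0.04 SD. The target is 0.017/0.058 = 0.293 SD, so this is about 7% to 14% of it. An unlucky imbalance of two standard errors (0.20 SD) would shift the estimate by 0.04 to 0.08 SD, or 14% to 27% of the target.

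**Step 5: is that variation already in the interval?** Yes. The unadjusted variance splits as 0.10² = (r × 0.10)² + 0.10² × (1 − r²). At r = 0.4 this is 0.0100 = 0.0016 + 0.0084. The first term is what adjustment removes, and the unadjusted confidence interval already includes it.

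**The case against.** The case against acting is substantial, and most of it stands.

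- **Validity.** A reader might infer that the PAEE comparison is biased without a baseline covariate. The documents do not support that: arms are randomised, and the rule's wording plainly anticipates outcomes with no baseline value.
- **Power.** A reader might infer that the trial is short of power for PAEE. Step 1 shows the opposite. The calculation never relied on adjustment.
- **Inconsistency.** Treating vitamin C differently is not a contradiction. One rule is applied to both outcomes, and only one has a baseline assay.
- **Imbalance.** It is tempting to set the 0.10 SD standard error of the baseline difference against the 0.29 SD target, as if a third of the target were at risk. Only the correlated part passes through (Step 4), and the interval already allows for it (Step 5).
- **Size of r.** The Background itself criticises self-report as inexact and prone to recall error, so a low correlation is plausible. The 0.67 for vitamin C is a test-retest value for one assay and cannot be borrowed for two different activity instruments.
- **Silence.** Only the stratifiers are expressly ruled out. An unseen analysis plan might add a covariate, and nothing suggests that baseline EPAQ-2 will go unreported.

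The last point does not remove the suggestion. The article states a covariate rule and its purpose, and that rule as written gives PAEE nothing although suitable data are collected.

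**Conclusion.** The point holds as a low-cost improvement, not as an error. Under the stated rule PAEE is analysed without any covariate, although a baseline measure of the same behaviour is available in both arms. The analysis remains valid and the stated power is met.

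The size of the missed gain rests wholly on an assumed correlation. It is negligible at 0.1, slight at 0.2 (about 1.5 points of power) and useful at 0.4 (about 6 points, equivalent to some 38 more participants per arm). The figures also assume 200 analysed per arm, an SD of 0.058, a two-sided 5% test and a roughly linear relation between the score and PAEE.

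**What to change.** Add one sentence to the Statistical analysis section: the PAEE regression will be adjusted for one baseline self-reported activity score, the EPAQ-2 summary score, using the missing indicator method already planned where it is absent. The article does not describe how EPAQ-2 is scored, so the score and its units should be named in advance. IPAQ should not be substituted where EPAQ-2 is missing, because that would put two scales under one coefficient. Report the chosen score by arm at baseline, as the available direct check on activity balance.

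The choice should be fixed before PAEE is compared by arm, since a covariate picked afterwards would invite criticism.

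The cost is two degrees of freedom (the score and its missing indicator) out of about 400 participants, with no new measurement. If the correlation proves low, little is gained and almost nothing is lost.

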2.2 What are the clinical consequences of behaviour change?

## Methods and Design

### Design and setting

The *ADDITION-Plus *study is nested within the intensive treatment arm of the *ADDITION-Cambridge *trial with additional practices (n = 8) added to increase the recruitment of recently diagnosed patients; see Figure 1 for details of study design and patient flows. Participants were recruited from 34 general practices in urban, suburban and rural Cambridgeshire, East Hertfordshire, West Suffolk and North Essex areas of England. 239/425 eligible screen-detected patients from *ADDITION-Cambridge *study, and 239/684 patients clinically diagnosed within the previous 3 years were individually randomised to receive intensive treatment alone or in conjunction with a facilitator-led behaviour change intervention.

Ethical approval was obtained from the Eastern Multi-Centre Research Ethics Committee (reference number: 02/5/54). Participants gave written informed consent to take part in the study. ISRCTN 99175498.

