### Intensive treatment (comparison arm)

The following features were added to routine multi-disciplinary primary care of diabetes to achieve intensive treatment in both trial groups:

1. Academic detailing for general practitioners and practice nurses: A practice-based academic detailing session for primary care teams was conducted by a local diabetologist or GP opinion leader to describe the treatment algorithms and targets, patient materials, and to present the evidence underpinning intensive treatment.

2. Treatment algorithms: These were based on trial data demonstrating the benefits of intensive treatment of several cardiovascular risk factors in people with diabetes [35-38], and recommended medication within licensed indications (Table 1). GPs were advised to consider prescribing an angiotensin converting enzyme (ACE) inhibitor to patients with a blood pressure≥120/80 and either a previous cardiovascular event or at least one other cardiovascular risk factor [39]. The remainder of the intervention was based on the stepwise target-led regimen from the Steno-2 study [23] aimed at optimising hyperglycaemia, hypertension, dyslipidaemia and microalbuminuria. GPs were advised to consider prescribing 75 mg of aspirin daily to patients without specific contraindications. Although targets for treatment were specified and classes of drugs recommended, where there was a choice between individual drugs the decision was made by the GPs and patients. The intensive treatment protocol was revised after publication of the Heart Protection Study [40] to include a recommendation to prescribe a statin to all patients with a cholesterol level of≥3.5 mmol/l.

**Table 1 T1:** Measures used at baseline and one year in the *ADDITION-Plus *trial (Cambridge, UK)

Measures	Baseline		One year	
	**C**	**I**	**C**	**I**

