### Sample size

The trial was designed within the main *ADDITION-Cambridge *trial. It was anticipated that 500 patients would participate in the *ADDITION-Plus *trial and that 200 individuals per group would be available with follow-up data. With these numbers, there is 80% power at the 5% level of significance level to detect the following relevant differences between arms in primary outcomes:

Physical activity:

A 0.017 kJ/kg/min difference in PAEE. This is based on a standard deviation of 0.058 at baseline in the *ProActive *trial dataset [72] with mean 0.078. A 0.017 absolute difference represents a 22% relative difference in mean energy expenditure between groups.

Diet:

A 5.5 umol/l difference in plasma vitamin C (control group mean 53, SD 19, EPIC study [73]). Adjustment for baseline level in the analysis allows a finer difference of 4.0 umol/l to be detected between arms (EPIC test-rest correlation of 0.67).

Medication adherence:

A 10% absolute difference in the proportion of low adherers to hypoglycaemic medications (control group 18%, Supported Adherence to Medication pilot study [51]).

Smoking:

A 9.5% absolute difference in the proportion smoking (control group 17.9%).

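### The supportive per-protocol analysis selects the intervention arm on session attendance and applies no comparable selection to controls, so it gives up the protection of randomisation

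*Protocol article*

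**What the plan says.** Under Statistical analysis, the protocol article gives the per-protocol analysis a supporting role on all primary outcomes: "The primary intention to treat analysis will be supported by per protocol analyses of primary outcomes". Membership is fixed by one rule: "the per protocol population is defined to be those participants attending the introductory and initial three core intervention sessions".

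The section on the intervention group places these sessions in the facilitator programme: "It included a one-hour introductory meeting followed by six 30-minute meetings and four brief phone calls". I take the core sessions to be the six 30-minute meetings. The same section says who gets the programme: "Participants in this group received intensive treatment (described above) plus a facilitator-led, individually tailored behaviour change intervention". What the comparison arm receives is listed under Intensive treatment (comparison arm), introduced by "The following features were added to routine multi-disciplinary primary care of diabetes to achieve intensive treatment in both trial groups". None of the eight listed features is a facilitator session. The trial randomises individuals, who were "individually randomised to receive intensive treatment alone or in conjunction with a facilitator-led behaviour change intervention".

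**The concern.** Attendance is observed after randomisation and can be seen in one arm only. Comparing attenders with all controls removes from the intervention arm the people who did not engage with a behaviour change programme. It leaves their counterparts in the control arm, because nobody can tell who they are.

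The four primary outcomes are activity, diet, medicine-taking and smoking. Willingness to attend sessions on these behaviours is plausibly related to the behaviours themselves, so the two groups could differ at one year even if the programme did nothing.

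What is at stake is interpretation. If the intention-to-treat result were null, a favourable attender comparison could be read as showing that the programme works in those who engage. The Discussion says that the results will inform policy on health trainer initiatives.

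**Working it through.** **Who can meet the rule.** The rule needs attendance at four facilitator sessions. The intervention arm is offered them. The eight features given to both arms do not include them. No other criterion for controls appears in the article. For the analysis to be a between-arm comparison, controls must therefore enter unselected.

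**What adjustment is available.** The Statistical analysis section adjusts continuous outcomes for their baseline value where it was measured, and does not adjust for stratifiers. In Table 1, plasma vitamin C is the only one of the four objective behaviour measures taken at baseline. Objectively measured activity, plasma drug levels and plasma cotinine are taken at one year only.

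**Illustration for smoking, no true effect.** Inputs:
- control prevalence 17.9% (Sample size section);
- attendance a, assumed 0.7 to 0.9;
- ratio k of smoking prevalence in non-attenders to that in attenders, assumed 1.5 to 3.

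The article gives neither a nor k. With no effect, prevalence in the whole intervention arm is also 0.179. If attenders smoke at p, then a·p + (1 − a)·k·p = 0.179, so p = 0.179 / (a + (1 − a)k).

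| a | k | p in attenders | Spurious difference |
|---|---|---|---|
| 0.9 | 1.5 | 0.179/1.05 = 17.0% | 0.9 points |
| 0.8 | 2 | 0.179/1.20 = 14.9% | 3.0 points |
| 0.7 | 3 | 0.179/1.60 = 11.2% | 6.7 points |

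The planned detectable difference is 9.5 points. The sign follows from k. At k = 1 the bias is zero. At k = 0.5 and a = 0.8, p = 0.179/0.90 = 19.9%, a spurious 2.0 points against the intervention.

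**How often this would look significant.** The Sample size section expects that "200 individuals per group would be available with follow-up data". In the central case, 160 attenders at 14.9% are compared with 200 controls at 17.9%. The standard error is √(0.149×0.851/160 + 0.179×0.821/200) = 0.039, so the expected z is 0.030/0.039, about 0.76. The two-sided 5% test then rejects in about 12% of trials. The mild corner of the table gives about 5.5% and the extreme corner about 42%.

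**Illustration for vitamin C, no true effect, before baseline adjustment.** Let q be the proportion attending, r the correlation of attendance propensity with vitamin C (both assumed), and SD = 19 umol/l (Sample size section). Then bias = r × SD × φ(z)/q, where z is the normal quantile at 1 − q.

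- q = 0.9, r = 0.1: 0.4 umol/l, rejection rate 5.4%.
- q = 0.8, r = 0.2: 0.2 × 19 × 0.280/0.8 = 1.3 umol/l, rejection rate 10%.
- q = 0.7, r = 0.3: 2.8 umol/l, rejection rate 27%.

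The planned detectable difference is 5.5 umol/l, or 4.0 after baseline adjustment. That adjustment would remove part of this bias.

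**Choice of threshold in a complier analysis.** Let a₁ be the proportion attending any session and a₄ the proportion attending all four. Let e₄ be the mean effect in those who attend all four and e₁ the mean effect in those who attend some sessions but not all four. With no effect in people who attend nothing, the intention-to-treat effect is a₄e₄ + (a₁ − a₄)e₁.

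- Four sessions as receipt: dividing by a₄ gives e₄ + e₁(a₁ − a₄)/a₄. This overstates e₄ whenever partial attenders benefit.
- Any session as receipt: dividing by a₁ gives the average effect among all who attended, without that excess.

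**The case against.** The strongest reply is that intention to treat is primary. No primary estimate, power figure or imputation scenario depends on the per-protocol population. This stands in full and limits the point to a supportive analysis.

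A reader might infer from the literal rule that the population contains none of the 239 comparison participants, so that no effect can be estimated. That reading is strained. The section describes analyses that compare the two groups, and a set without controls could not support such a comparison. The natural reading is that attendance defines adherence in the intervention arm and that all controls stay in. A condensed article could leave that clause to the full plan. Stating the clause would not remove the selection problem, though, because the rule that the article fixes still filters one arm only.

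A reader might also infer that the bias certainly favours the intervention, or that it would produce effects on every primary outcome. The article reports no attendance rate and does not compare attenders with non-attenders. People who already felt well controlled might also stop coming. A range of ratios above 1 builds in the sign, and even then the central smoking case rejects only about 12% of the time.

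Finally, the article speaks of change from baseline in smoking status, and self-reported smoking is recorded at baseline. If change is what is analysed, part of the smoking bias would go. This is uncertain: the method named for binary outcomes is a comparison of proportions, and cotinine has no baseline value. The case is firmest for activity and drug levels, although those are not the outcomes illustrated above.

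**Conclusion.** The point holds as a should-fix on a supportive analysis. The per-protocol rule compares participants selected after randomisation with unselected controls. Little in the planned adjustment corrects this for three of the four objective outcomes. That conclusion rests on the text alone.

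The size and direction rest on assumed attendance and on an assumed link between attendance and outcome. Under those assumptions the spurious smoking difference is 0.9 to 6.7 points (3.0 in the central case). The unadjusted vitamin C bias in the cases shown is 0.4 to 2.8 umol/l. Bias towards the intervention is likely but not established. The documents do not support any doubt about the intention-to-treat result on this ground.

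**What to change.** Make the supportive analysis a complier-average causal effect: two-stage least squares, randomised arm as instrument, and the same covariates as the intention-to-treat model. Binary outcomes can be estimated on the risk-difference scale.

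- Define receipt in the main version as attending any facilitator session. The exclusion restriction is more credible there.
- Report the introductory-plus-three-sessions threshold as a sensitivity analysis, and say that it overstates the effect if partial attenders benefit.
- Check that no comparison participant had facilitator sessions. One-sided non-compliance follows from the design, but the article does not discuss crossover.
- If the attender comparison is kept, state that all controls are included and label it non-randomised and exploratory.

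The cost is a change of wording and a little code, using attendance data that the present rule already needs. The drawbacks are a wider interval than the attender comparison would give and an exclusion restriction that must be stated and defended.
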